## Methods/design

The EoP scheme was evaluated in a randomized trial conducted in 2005–2006 with two groups: EoP and control patients. The EoP scheme was launched one year prior to the evaluation and offered by the County of Ribe and the County of Vejle. Patients were referred to the EoP scheme by their GP. GPs act as gatekeepers in the Danish health care system [19].

The motivational counselling and the group-based supervised training intervention in EoP patients were carried out by a physiotherapist in 14 clinics geographically spread throughout the two counties.

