### Recruitment and allocation

Referred patients contacted an EoP clinic, and an appointment for the first health profile was scheduled (Figure 1). All patients referred to the EoP scheme were eligible for the trial and were offered participation in the randomized trial during the baseline health profile. Recruitment took place over 14 months in 2005 and 2006.

Informed consent was obtained, and volunteering patients were randomized to either the EoP group or the control group. Randomization was carried out by the first authors by means of concealed envelopes containing the name of the group. Group allocation was then reported by mail to the physiotherapist and the patient. Randomization was stratified according to diagnosis (cardiovascular diseases, metabolic syndrome, type II diabetes, and other diseases) in order to distribute diagnosis groups evenly in the two groups.

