### Sample size

Power calculations were performed for expected changes in VO_2_max. VO_2_max at baseline was estimated to 20 ml O_2_*(min*kg)^-1^, expected improvements were 15%, and expected SD was 3 ml O_2_*(min*kg)^-1^. Alpha was set at 0.05 and a power of 0.9 was chosen. Using these assumptions in the 'sampsi' command in Stata 9.0 the sample size was estimated to 22 in each group.

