### Statistical analysis

The changes from 0–4 and 0–10 months within the two groups separately will be assessed using paired t-test or Wilcoxon rank sum test depending on distribution. Furthermore, boxplots will be made for delta values for the changes from 0–4 and 0–10 months.

Comparisons between the EoP group and the control group will be made with changes from 0–4 and 0–10 months. The analysis will be performed as an intention-to-treat and carried out using a regression model incorporating delta values, controlling for baseline values, and adjusted for the effect of the different centres (physiotherapist clinics), further robust variance will be applied. For variables not fulfilling the normal distribution of residuals a Wilcoxon rank sum test will be used on delta values. These analyses will be supplemented with 'per protocol analyses'.

Drop-out analyses will be carried out for 0–4 months and 4–10 months. Completers and non-completers will then be compared for the different baseline variables using boxplots. The effect of drop-out will be compared with differences between the EoP group and the control group.

Statistical significance was set at p < 0.05.

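### Randomisation is stratified by diagnosis, but the between-group model and the fallback rank test leave diagnosis out, so inference may be conservative and some precision forgone

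*Protocol article*

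**What the plan says.** Recruitment and allocation names one stratification factor: "Randomization was stratified according to diagnosis (cardiovascular diseases, metabolic syndrome, type II diabetes, and other diseases". Its stated purpose is "in order to distribute diagnosis groups evenly in the two groups". Allocation was done "by means of concealed envelopes containing the name of the group"; blocking within strata is not mentioned.

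Statistical analysis sets out the between-group comparison of changes over 0–4 and 0–10 months. The regression is described as "controlling for baseline values, and adjusted for the effect of the different centres (physiotherapist clinics", with robust variance. The fallback is: "For variables not fulfilling the normal distribution of residuals a Wilcoxon rank sum test will be used on delta values". Diagnosis appears in neither.

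Clinic, which is adjusted for, is not named as a stratification factor. According to Methods/design, the intervention was "carried out by a physiotherapist in 14 clinics geographically spread throughout the two counties".

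**The concern.** When allocation is balanced within strata, differences between diagnosis groups are largely removed from the comparison of the arms. If the model leaves diagnosis out, those differences stay in its residual error. The standard error then describes a noisier comparison than the one the design produced. Robust variance does not repair this, because it is computed from the same residuals and does not use the strata.

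Confidence intervals would be somewhat too wide, the true type I error would fall below the nominal 5%, and some power would be given up. It is plausible that change in fitness, weight or HbA1c differs between cardiovascular, metabolic syndrome, diabetic and other patients, since diagnosis is the one factor the trial chose to balance. The documents do not say how much it differs.

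**Working it through.** **Inputs.** From Sample size: "VO_2_max at baseline was estimated to 20 ml O_2_*(min*kg)^-1", an expected improvement of 15% (0.15 × 20 = 3), SD 3, alpha 0.05, power 0.9, 22 per group. From Methods/design: 14 clinics. From Recruitment and allocation: four strata. The share R² of the variance of change that diagnosis explains beyond baseline value and clinic is not given. It is an assumption here, varied from 0 to 0.30.

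**Step 1: the plan's own figure.** n = 2 × (1.95996 + 1.28155)² × 3²/3² = 21.01, rounded up to 22 per group (two-sided). The stated sample size reproduces, and this point does not affect it. Power at 22 per group is 0.913 by normal approximation.

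**Step 2: effect of leaving diagnosis out, without clinic terms, strata balanced.**
- Reported SE without diagnosis: 3 × √(2/22) = 0.905 (0.9045 unrounded).
- True SE, which is also the reported SE with diagnosis in the model: 0.9045 × √(1 − R²). At R² = 0.10 this is 0.9045 × 0.9487 = 0.858.
- Excess width: 1/√(1 − R²) − 1.
- True type I error without diagnosis: 2 × [1 − Φ(1.96/√(1 − R²))].
- Power without diagnosis: Φ[(3 − 1.96 × 0.9045)/true SE]. Power with diagnosis: Φ[3/true SE − 1.96].

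| Assumed R² | True SE | Reported SE too wide by | Type I error without diagnosis | Power without / with diagnosis |
|---|---|---|---|---|
| 0 | 0.905 | 0% | 5.0% | 0.913 / 0.913 |
| 0.05 | 0.882 | 2.6% | 4.4% | 0.918 / 0.925 |
| 0.10 | 0.858 | 5.4% | 3.9% | 0.924 / 0.938 |
| 0.20 | 0.809 | 11.8% | 2.8% | 0.935 / 0.960 |
| 0.30 | 0.757 | 19.5% | 1.9% | 0.948 / 0.977 |

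**Step 3: closer to the planned model.** The simulation used 44 patients, clinic indicators for 14 clinics, robust (HC1) variance, four strata of 30/30/20/20%, SD 3, a difference of 3 and 1,500 trials per setting. Baseline value was not simulated; R² stands for what remains after it. Each pair is without / with diagnosis.

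| R² | Type I, blocks of 4 | Power, blocks of 4 | Type I, no blocking | Power, no blocking |
|---|---|---|---|---|
| 0 | 4.7% / 4.9% | 0.746 / 0.726 | 4.6% / 5.4% | 0.747 / 0.694 |
| 0.05 | 4.0% / 4.0% | 0.757 / 0.753 | 4.6% / 4.3% | 0.744 / 0.721 |
| 0.10 | 3.9% / 5.2% | 0.761 / 0.769 | 5.8% / 6.2% | 0.729 / 0.747 |
| 0.20 | 4.3% / 4.7% | 0.758 / 0.813 | 4.7% / 4.7% | 0.735 / 0.776 |

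The simulation error is about 0.6 points for type I error (√(0.05 × 0.95/1500)) and 1.1 points for power (√(0.75 × 0.25/1500)), so small differences should not be read closely. Repeat simulations of this design gave, with blocking, power of 0.736 / 0.725 and 0.713 / 0.705 at R² = 0, and 0.736 / 0.798 and 0.746 / 0.801 at R² = 0.20. Without blocking at R² = 0, a repeat gave 0.736 / 0.687.

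Power here is below 0.913 because many clinic terms are fitted in 44 patients. That applies to both models and is not part of this point.

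**Step 4: a larger trial.** With an illustrative 120 patients, blocked strata, R² = 0.20 and a difference of 1.8, the reported SE without diagnosis averages 0.582 against an actual 0.522. Type I error is 2.9% / 5.2% and power 0.899 / 0.942. At R² = 0, power is 0.861 / 0.862, so the cost of the extra term has disappeared.

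**The case against.** The strongest reply is that both conditions for the problem are unproven. No figure in the article shows that diagnosis predicts change beyond baseline value and clinic. Nor is blocking stated, and simple randomisation within each stratum gives no more balance than no stratification. Without blocking, Step 3 finds the planned test close to its nominal 5%. This stands, and it is why the point is conditional. It does not remove the point: the stated aim of an even spread makes some restriction within strata likely, and without blocking power is still lost at R² = 0.20 (0.735 against 0.776).

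Second, at 22 per arm with 14 clinics the extra term is not free. It loses power if diagnosis explains nothing, and with blocking it does not help until R² is about 0.10. This also stands and belongs in the cost.

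Third, any error is in the safe direction: no bias and no excess of false positives. This stands and limits the weight of the point.

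Fourth, adjusting for clinic is reasonable even though clinic was not a stratifier, because training and measurement both take place there. That is right. The point is that diagnosis is absent, not that clinic is present.

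It could also be said that an article leaves such detail to the full plan. Here, however, the article lists its adjustment terms, so the mismatch lies in what is stated.

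**Conclusion.** The point holds in conditional form. The stated analysis omits the one factor the trial randomised by. If diagnosis predicts change beyond baseline value and clinic, and the arms are balanced within strata, the reported standard error is too wide by about 5% at R² = 0.10 and 12% at R² = 0.20, before clinic terms. With clinic terms at 44 patients, adding diagnosis raises power by about 5 to 6 points at R² = 0.20 when strata are blocked.

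A reader might infer more: that the standard errors are simply too wide, or that the benefit of stratifying is lost. The documents support neither. They give neither the explained share nor the blocking, and at R² = 0 nothing is lost. The balance that stratification was meant to secure is kept whatever the model, the estimate stays unbiased, and its true variance is still reduced. In Step 2, power without diagnosis rises from 0.913 to 0.924 at R² = 0.10, against 0.938 with it, so only part of the gain is forgone. The right label is a cheap improvement.

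**What to change.** In Statistical analysis, add the four-level diagnosis stratum, as used at randomisation, as a covariate in the between-group regression models. For HbA1c, which is measured only in patients with reduced insulin sensitivity, include only the strata present in that subset. Replace the unstratified between-group rank sum test with one stratified by diagnosis, such as the van Elteren test. Also state whether the envelopes were blocked within strata, since the size of the effect depends on it.

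No new data are needed, because the stratum had to be known to allocate each patient. The cost is 3 degrees of freedom. At 22 per arm with 14 clinic terms, if diagnosis explains nothing, this loses about 1 to 2 points of power with blocked strata (0.746 to 0.726, 0.736 to 0.725, 0.713 to 0.705) and about 5 without blocking (0.747 to 0.694, 0.736 to 0.687). In a larger trial the cost is negligible. The change should be fixed before the outcome data are analysed.

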### Outcome measures

The EoP physiotherapists carried out both the physiological and patient-reported measures. Changes in physiological measures (VO_2_max, bodyweight, BMI, and HbA1c) and patient-reported measures (physical activity, health-related quality of life, amount and intensity of exercise, compliance with national guidelines for physical activity, and self-reported physical fitness) were assessed at the time of the health profiles (Figure 1).

*Maximal oxygen uptake (VO_2_max) *was measured using a maximal indirect cycle ergometer test modified from Pedersen & Nielsen [21], where VO_2_max was calculated from the maximal work capacity (Wmax). All tests were completed on a mechanically braked cycle ergometer (Ergomedic 874E or 828E, Monark, Varberg, Sweden). Rate of perceived exertion was evaluated using the 6–20 point Borg scale [22]. Heart rate was measured using a telemetric system (Polar Vantage NV, Polar Electro KY, Kempele, Finland). Each workload consisted of three minutes of cycling at 60 rpm. A choice of two protocols was available: 1) an initial workload of 30 watts and increments of 30 watts until exhaustion (classic protocol), 2) an initial workload of 30 watts and increments of 60 watts until the subject rated perceived exertion ≥ 13 (somewhat hard). Thereafter increments of 30 watts were used until exhaustion (progressive protocol). The test was continued until the subject was unable to maintain a pedal frequency of 60 rpm despite verbal encouragement. Workload, maximal heart rate and total time were recorded, and Wmax and VO_2_max were calculated.

*Glycosylated hemoglobin (HbA1c) *was measured in capillary blood using the DCA 2000+ (Bayer Diagnostics Europe Ltd., Dublin, Ireland), and was only assessed in patients with reduced insulin sensitivity. HbA1c is an indicator of mean blood glucose level over the last 8–12 weeks and indirectly a measure of glycemic control [23]. In a comparison between DCA 2000+ and the gold-standard technique in HbA1c assessment the correlation was above 0.9, and the test-retest reliability with the DCA 2000+ was above 95 % [24,25].

*Bodyweight *was measured prior to the cycle ergometer test with patients wearing light clothes and no shoes using a commercial scale.

*Body Mass Index (BMI) *was calculated by dividing bodyweight with height squared.

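### No primary outcome or visit is named: 18 to 28 between-group tests share one p < 0.05 rule, although the trial is sized on VO2max alone and for no stated visit

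*Protocol article*

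**What the plan says.** The aim, at the end of the Background, lists four physiological and five patient-reported variables side by side, to be assessed at four and at ten months. Outcome measures repeats the list, from "Changes in physiological measures (VO_2_max, bodyweight, BMI, and HbA1c" through to "compliance with national guidelines for physical activity, and self-reported physical fitness) were assessed at the time of the health profiles". Neither place ranks the outcomes or the visits.

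Statistical analysis says: "Comparisons between the EoP group and the control group will be made with changes from 0–4 and 0–10 months". The between-group model is intention-to-treat, with per-protocol analyses as a supplement. The section also plans paired tests within each arm. Its only decision criterion is "Statistical significance was set at p < 0.05".

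Sample size rests on one outcome: "Power calculations were performed for expected changes in VO_2_max". The inputs are a baseline of 20 ml/(min·kg), with "expected improvements were 15%, and expected SD was 3 ml O_2_*(min*kg)^-1", and "Alpha was set at 0.05 and a power of 0.9 was chosen". The result is 22 per group. The section does not say whether the expected improvement refers to month 4 or month 10.

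**The concern.** A protocol should make clear which comparison decides whether the intervention worked. Here one outcome determines the size of the trial, but the analysis text gives it no special role. Every outcome at both visits meets the same threshold, so a low p-value on a single questionnaire item could be reported on the same footing as VO2max, even if VO2max showed nothing.

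The Discussion says that the trial feeds a health technology assessment, so the strength of any claim of effect matters. With many unranked tests at 0.05, the chance that at least one reaches significance by luck is far above 5%. A reader of the results could not tell a planned lead finding from a selected one.

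**Working it through.** **Step 1. Reproduce the sample size.** The difference is 15% of 20 = 3 ml/(min·kg), the SD is 3, alpha is 0.05 and power is 0.90.

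n = 2 × (1.960 + 1.282)² × (3/3)² = 21.01, rounded up to 22 per group. This matches the article. A one-sided test gives 18, so the calculation was two-sided. It covers one outcome at one visit.

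**Step 2. Count the between-group tests.**
- Domains as the aim lists them: 4 physiological + 5 patient-reported = 9. Two visits give 18 tests.
- Scores as Outcome measures describes them: 4 physiological + 1 physical activity + 2 SF-12v2 + 1 EQ-5D + 2 exercise questions + 1 guideline question + 3 fitness questions = 14. Two visits give 28 tests.
- The article does not say how many scores SF-12v2 and EQ-5D yield, so two and one are assumptions. With one SF-12v2 score the count is 13, or 26 tests.

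**Step 3. Chance of at least one false positive if EoP affects no outcome and the tests are independent.** For k two-sided tests at 0.05, the chance in either direction is 1 − 0.95^k. Each test has 0.025 in the direction favouring EoP, so the chance of at least one such result is 1 − 0.975^k.

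| Count | k | Either direction | Favouring EoP |
|---|---|---|---|
| 9 domains | 18 | 60.3% | 36.6% |
| 13 scores | 26 | 73.6% | 48.2% |
| 14 scores | 28 | 76.2% | 50.8% |

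The expected number of false positives among 28 tests is 28 × 0.05 = 1.4 in either direction, or 28 × 0.025 = 0.7 favouring EoP.

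**Step 4. Allow for correlation.** The article gives no correlations, so these are assumptions: 0.5 between visits, 0.98 between weight and BMI, and 0, 0.3 or 0.5 between other outcomes. The results come from simulating 400,000 sets of normal test statistics.

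| Count | Correlation between outcomes | Either direction | Favouring EoP |
|---|---|---|---|
| 14 scores | 0 | 74% | 48% |
| 14 scores | 0.3 | 64% | 35% |
| 14 scores | 0.5 | 53% | 28% |
| 9 domains | 0 | 58% | 34% |
| 9 domains | 0.3 | 49% | 26% |
| 9 domains | 0.5 | 42% | 21% |

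**Step 5. After the fix.** One named primary test carries 5% (2.5% favouring EoP), with n unchanged at 22. VO2max at both visits without adjustment would carry 1 − 0.95² = 9.75% if independent. Splitting alpha, 0.025 per visit, needs 2 × (2.241 + 1.282)² = 24.8, that is 25 per group.

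**The case against.** A reader might infer that 76% is the chance of falsely concluding that EoP helps. The article does not support that. Its sample size reproduces only with a two-sided test, and 76% counts differences in either direction. For a difference favouring EoP the figure is 51% for 28 independent tests and 37% for 18.

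Independence is also the high end. Weight change and BMI change are nearly the same test, because BMI is weight divided by height squared and adult height is fixed. Both visits share one baseline. Step 4 shows how far this can bring the figures down.

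A reader might also say that the article has no lead outcome at all. That goes too far. VO2max is the only outcome powered and comes first in the lists, so it is an implicit lead that the text does not declare. Nor should the within-arm tests or the per-protocol analyses be added to the count. The former do not compare EoP with control, and the latter are a stated supplement to the intention-to-treat analysis. Reporting both weight and BMI is a minor matter of presentation.

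Finally, a detailed multiplicity scheme may sit in a full protocol or analysis plan that is not shown. So it cannot be said that none exists. This does not settle the main point. The primary outcome and its visit are core design items that a protocol article normally states, and this one does state alpha, power, the model and the threshold.

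**Conclusion.** The point holds in this form: the article applies p < 0.05 to every outcome at two visits and names no primary outcome or visit, while its sample size rests on VO2max at an unstated visit.

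If the text is followed as written and EoP has no effect, the chance of at least one significant between-group difference is at most about 60–76% in either direction, or about 37–51% favouring EoP. These are the values under independence, and they are lower with positive correlation. Across the correlations tried, the chance of a result favouring EoP was 21–48%, against 2.5% for a single named two-sided test.

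The range rests on counting 9 to 14 outcomes, on the assumed number of quality-of-life scores, and on the assumed correlations. The missing primary outcome and visit can be read directly from the text and depend on none of these.

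**What to change.** State in Statistical analysis that the primary comparison is the between-group difference in VO2max change at one named visit, for example 0–4 months, at two-sided 0.05. Test VO2max change at the other visit at 0.05 only if the first is significant. Report all other outcomes as supportive estimates with 95% confidence intervals and no claim of significance. Name the same visit in Sample size.

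The choice of visit needs a sentence of justification, because the aim gives four and ten months equal standing. The article describes the trial as conducted in 2005–2006, so the choice should be dated and made without sight of results by group.

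The sample size stays at 22 per group. The costs are:
- No confirmatory claim on any outcome other than VO2max.
- Somewhat lower power at the gated visit. If each visit has 90% power and they are independent, it is 0.9 × 0.9 = 81%; it is higher if they are positively correlated.

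If the two visits must stand equally, splitting alpha between them is an alternative, at 25 per group.

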### Approval

Local ethics committee registration number VF 20040121. The Danish Data Protection Agency registration number 2004-41-4692. ClinicalTrials.gov registration number NCT00399997.

### Validation studies

Validation studies were carried out for the cycle ergometer test, the HbA1c method, and the self-administered questionnaire. Detailed information about the validation studies can be found in the appendix.

### Wmax cycle ergometer test validation

Validation was performed for both the calculation of VO_2_max from Wmax (equation study) and the comparison of the two different protocols (protocol study). The protocol study aimed at finding a less time-consuming protocol, and evaluating test-retest reliability.

A close relationship between Wmax and VO_2_max in a group of EoP patients (Figure 2) and acceptable test-retest reliability at group level (Figure 3, right) were found. Furthermore, results from the two different protocols were comparable at group level (Figure 3, left). However, at individual level the Wmax test was less reliable.

**Figure 2 F2:**
[figure not shown]
The Wmax-VO_2_max relationship. The maximal work capacity (Wmax) was plotted against the maximal oxygen uptake (VO_2_max), and linear regression was performed. The relationship was highly linear (VO_2_max = 13.895 * Wmax + 151 ml O_2_/min, R^2 ^= 0.9108, p < 0.0001), but prediction intervals were wide (mean ± 1.96 SD, 452 ml O_2_/min).

**Figure 3 F3:**
[figure not shown]
Differential plots with limits of agreement (LOA) for the classic test vs. the progressive (left) test and 1st test vs. 2nd test (right). The individual differences for the two tests were plotted against the individual mean of the two tests. Furthermore, limits of agreement (LOA) were calculated and plotted (dotted lines). LOA was wide in both comparisons (29.6 watt and 28.6 watt, respectively), but no statistical significant differences were found. In both cases coefficient of variation was 6.95%.

